## Abstract

**Background:**

The top-down cognitive and emotional control skills known as Executive Function (EF) and Self-Regulation (SR) have a large impact on everyday life. As a schoolchild, you are expected to pay attention, wait your turn, follow instructions, solve academic problems and be creative while navigating the social space of peers and teachers. All these abilities draw on EF and SR. Research has pointed to curricular programs as a promising path to build capacity in schoolteachers and provide with further knowledge on ways to support and strengthen these EF and SR skills in their pupils through activities, strategies and reflection tasks. The importance of EF and SR on later life outcomes such as academic performance, career, relationships and risk of crime, has been a motivating factor to develop the 10-session On Track 2.0 intervention as a universal whole-class approach to improve EF and SR in primary school pupils.

**Methods:**

Regular 4th and 5th grade class groups will be invited to participate in this teacher-delivered intervention program to be implemented into regular lessons. In this study schools will be randomly assigned to either intervention or control group as part of a cluster-randomized controlled trial. Psychometric and questionnaire assessing EF, SR and well-being will be administered to children, teachers and parents at three time points.

**Discussion:**

The intervention holds the potential to support and qualify teachers in understanding students’ challenges with EF and SR better and in training these skills during class. A multimodal and multi-informant approach to assessment, in addition to data on teacher adherence and platform use, will aid the insight into the efficacy of the intervention content and delivery.

**Trial registration:**

The study has been registered at Open Science Framework on 22 January 2025.

## Introduction

1

This study protocol is for a cluster-randomized controlled trial (RCT) of On Track 2.0, a classroom-based teacher-delivered intervention to support and improve executive function for Danish schoolchildren in 4th to 5th grade. The intervention content and design are based on a previous feasibility testing and pilot project of On Track in four Danish primary schools.

Executive Functions (EF) are higher-order functions that refer to conscious top-down cognitive control and enable self-regulation of thoughts, feelings and behavior (Zelazo and Carlson, 2012). EF are applied with a conscious effort when habit and automatic actions are insufficient or inappropriate (Diamond, 2013). Many definitions of EF exist, however there is general agreement that they include the three subdomains of response inhibition (inhibitory control), working memory and cognitive flexibility (or shifting) (Diamond, 2013; Miyake and Friedman, 2012). In combination, these skills enable complex cognitive abilities such as planning, organization, metacognition and self-reflection (Dawson, 2021; Dawson and Guare, 2014). In their study on the unity and diversity of EF, Friedman and Miyake (2017, p. 194) found that the common factor across the three EF subdomains was “the ability to maintain and manage goals and use those goals to bias ongoing processing.” Though this ability is central to inhibition tasks, it is required in all EF tasks (Friedman and Miyake, 2017). This understanding can be conceived as the ability to stay on track and is closely related to other cognitive phenomena such as focused attention and the more colloquial term “concentration.” Focused attention is generally defined as the voluntary act of attending to certain stimuli while ignoring others (Posner and DiGirolamo, 1998), while concentration is defined as the ability to sustain attention and is closely connected to EF such as working memory (Avisar, 2023). Friedman et al. (2007) confirmed the theoretical prediction that attention problems primarily arise due to a deficit in response inhibition. Following from here, the terms concentration and focused attention may be thought of as the foundation for maintaining and managing the above-mentioned goals by supporting and being partly overlapping with inhibition, the common EF factor, thereby enabling successful executive functioning in general.

Related to EF, but not overlapping is self-regulation (Hofmann et al., 2012). SR entails being able to delay instant gratification and stop unwanted impulses in order to pursue long-term goals (Haywood and Lidz, 2006). A pursuit that does not come without the need to regulate and control emotions and frustration. EF have been highlighted as the foundation and prerequisite for successful SR, indicating that efforts to improve EF have the potential to support SR too (Hofmann et al., 2012; Rueda et al., 2005).

Executive function begin to emerge during infancy and develop throughout childhood and have proved to be essential to school success and a range of other life outcomes (Diamond, 2013; Moffitt et al., 2011). Even though EF are not fully mature until adulthood, EF early in life are highly predictive of EF skills later in adolescence and adulthood (Diamond, 2016). In addition, children with poor EF were found to be far less likely to graduate from high school (Diamond and Ling, 2019; Moffitt et al., 2011).

Recent studies suggest that the emotional and cognitive control of adults such as parents and teachers are critical for the caregiving practices involved in children’s EF development (Bardack and Obradović, 2019). A longitudinal study on parental scaffolding practices found that verbal and physical interaction to support the child in solving a ring puzzle task at age 3 were predictive of child EF at age 4 (Hammond et al., 2012). In an observational study, Bardack and Obradović (2019) found that teachers’ display of EF difficulties negatively predicted the assessment of students’ EF skills. These associations underline the potential of designing and providing professional development for teachers focusing on building EF knowledge and scaffolding strategies.

Despite their importance for academic performance and social well-being, EF skills are rarely addressed or listed explicitly in curriculum standards (Dawson, 2021). Systematic reviews and meta-analyses have shown that school-based interventions can improve EF (Diamond and Ling, 2019) and that teacher-student interactions are important for children’s performance in EF (Vandenbroucke et al., 2018). According to Diamond (2016) improving EF may be critical to long-term happiness and life success, and schools and institutions provide a unique place to offer universal efforts and approaches to the benefit of all children in a class group. It is important for interventions to be cognitively engaging, progressively more challenging and personally meaningful to the participants (Diamond and Ling, 2019). However, results from intervention studies are often limited to near-transfer task improvements rather than more global improvements on EF and academic skills across contexts (Melby-Lervåg et al., 2016; Shipstead et al., 2012).

In the autumn of 2022, we piloted the On Track project in 13 classrooms across four randomly selected schools in Zealand, Denmark. The intervention consisted of three researcher-led workshops conducted 2–3 weeks apart in 4th to 6th grade classrooms. The Departmental Ethics Committee approved the project, and participants with parental consent took part in assessments prior to and following the intervention. A combination of the psychometric concentration test d2-R and the Strengths and Difficulties well-being questionnaire was used in addition to a written evaluation interview with closed and open questions. The design did not include a control group making it difficult to draw firm conclusions, but pre-to post-measures improvements exceeded expected retest scores substantially, and the evaluation forms conveyed general contentment with the intervention concept, content and outcome.

The On Track 2.0 intervention program aims to support and train EF in primary school children through educator-led activities integrated into the curriculum. A comprehensive systematic review by Diamond and Ling (2019) highlights that school programs are among the most effective methods for improving EFs. In addition, educator capacity is vital (Muir et al., 2024) and offering further training to teachers significantly increases the likelihood of fostering sustainable changes compared to having activities delivered by outside experts. This approach enhances the opportunity for educators to take ownership of the content and empower them to apply the material in accordance with the strengths and challenges in their specific class groups (Bundsgaard et al., 2018; Muir et al., 2024). In 2023, the amount of Danish early school leavers was higher than 10 years earlier and above the EU average (Eurostat, 2024). According to a recent report, around 15% of 25-year-olds in Denmark have completed only lower secondary education and are not enrolled in an education (Kraka Advisory, 2023). The report concludes that the societal costs associated with the expected loss in earned income is equivalent to about 107 billion Danish kroner (~€14,3 billion) per year group (Kraka Advisory, 2023). The fact that improved EF and SR have a potential positive impact on individual mental health and interpersonal behaviors (Robson et al., 2020) but also high personal and societal costs and justify and encourage further research in interventions to support and train these skills.

On this foundation, we have designed an intervention aimed at improving core EF domains and well-being. Compared to other interventions addressing EF (Diamond and Ling, 2019) On Track 2.0 is novel in its approach as teachers can access and implement the intervention without researcher assistance and interference. The preparation time is minimal, with teacher informational podcasts and pupil activities tapping into core aspects of EF and SR gamified through the story about detective Sofus trying to solve a mystery. Whereas many interventions developed to support EF target pre-school aged children, On Track 2.0 is designed for children in late primary school, addressing a research gap in the (Jacob and Parkinson, 2015) with the potential to help more children to thrive in and outside of school settings.

The goal of improving EF and well-being through On Track 2.0 is explored through the following four research questions (RQs):

RQ1a: Can the On Track 2.0 intervention improve EF in Danish 4th and 5th grade pupils from pre-to post-intervention assessment?

RQ1b: Is the potential EF improvement of the On Track 2.0 intervention sustained until or increased at the follow-up assessment?

RQ2a: Can the On Track 2.0 intervention improve child-reported well-being in Danish 4th and 5th grade pupils from pre-to post-intervention assessment?

RQ2b: Is a potential improvement in well-being sustained at the follow-up assessment?

In addition, we will explore the following research questions:

RQ3: Do mechanisms such as age, gender, dosage or baseline performance affect either outcome?

RQ4: Does the intervention affect other variables measured such as subdomains of the psychometric tasks (d2-R and Stop Signal Task) or parent-and teacher-reported EF and well-being?

The following sections detail the intervention design, content, and assessment methods and strategies employed to ensure adherence and minimize bias.

On Track 2.0 is a 10-week cluster-randomized, teacher-led intervention integrated into regular classroom teaching. The target group is 4th and 5th grade pupils at standard Danish primary schools. Following the recommendations by Campbell et al. (2000) for complex health interventions, the study consists of four distinct phases. Based on a solid theoretical foundation, Phase I involves designing, modeling and qualitatively testing the content and details of the intervention. During this phase, editors at publishing company Forstå, who provide freely available online teaching materials to schools, assist practically with designing and setting up the intervention content on the online platform while offering didactical feedback.

Phase II entails an exploratory trial, which will include a design and feasibility testing involving a small number of classrooms. Different variations of the content may be tested and focus group interviews with teachers and pupils will inform the adaptation of the material prior to the RCT.

Following this stage, we will recruit schools and implement the definitive intervention in a cluster RCT. In Phase III intervention and teaching-as-usual control groups will be randomized on the school level to avoid contamination between class groups within schools. Control groups will be offered access to the intervention materials as soon as all assessments are completed in their group. For practical reasons, we plan to run the intervention in two waves (Wave 1 in the spring, and Wave 2 in the autumn), testing intervention and control groups in parallel.

Phase IV involves the transition from testing the materials to making them freely available to all teachers and promoting implementation in schools across the country. Results will be disseminated in academic journals but also to teachers and practitioners through targeted publications and presentations.

Many research studies have found that the continued implementation of evidence-based mental health interventions often face common barriers such as lack of teacher support, difficulties obtaining materials, and finding the time amongst many other obligations and priorities (Locke et al., 2015). To avoid similar challenges, more evidence-based teaching materials should be made freely available and easy to access and implement into standard classroom settings without the need to acquire new equipment (Banerjee et al., 2023).

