### General description of assessments

2.5

Researchers and research assistants will conduct assessments in the participating schools at three time points; t_0_: 1–2 weeks prior to the intervention period, t_1_: 1–2 weeks after the intervention period, and t_2_: 4 months after the intervention period (follow-up assessment). During assessments, pupils will complete psychometric tasks and questionnaires on iPads in a room where there is space between them and minimal visual and auditory distractions. Parents and teachers will receive secure links to their questionnaires, which they can complete privately at home.

Assessments will be conducted on-site at the schools involved in the project, and intervention and control groups will be tested in parallel. Whenever possible, research assistants who are blinded to the group allocation will conduct the data collection to minimize the potential risk of bias (Higgins and Cochrane Collaboration, 2020). For practical reasons, it will not be possible to blind main researchers and participating teachers to group allocation. However, because regular teachers will implement the materials into their own classes over 10 weeks, the risk of Hawthorne effects is expected to be smaller compared to researcher-led interventions (Murnane and Willett, 2011). To enhance study validity and reliability, more than one mode of assessment is used (multi-modal), multiple informants report on each child (multi-informant) and these informants represent different contexts from the child’s everyday life (multi-setting) (Sparrow, 2010).

To ensure ethical research practices during assessments, researchers and research assistants will talk to children in a developmentally appropriate language, thereby obtaining informed consent in a manner aligned with their understanding and developmental level (Field Marilyn et al., 2004).

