**Figure 1 fig1:**

Intervention and assessment timeline.

Baseline assessments take place immediately before the intervention (t_0_) and post assessments immediately after (t_1_) as mentioned above. Follow-up assessments (t_2_) take place 3-4 months after intervention completion.

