### Recruitment and randomization

2.10

Schools will be invited to participate through a combination of e-mails, newsletters and social media to teachers and school principals across the country. Representativeness of the participants is crucial to the external validity of the intervention (Glasgow et al., 1999). We plan to recruit schools from diverse municipalities, which will be randomized into intervention and teaching-as-usual waiting list control groups using a computer-generated random sequence unavailable to those enrolling and assigning schools. All recruited schools will be randomly allocated to avoid skewing results by including a highly motivated experimental group (Conrad, 1987). Ideally, to minimize bias, both program providers (teachers) and pupils should be blinded to whether they are in a treatment or control group (Schulz and Grimes, 2002). While complete blinding is challenging to achieve in psychological intervention studies, every effort well be made to maintain objectivity in the process. When including a waitlist control group, blinding teachers is not feasible to achieve. However, data collection and analyses will be conducted by different people, and analyses will be conducted on anonymized data by a researcher, who is blinded to group membership.

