### Data analysis

2.13

Statistical analyses will be conducted to examine the effects of the On Track 2.0 intervention. Descriptive analyses will be conducted of pupil, classroom, and school characteristics and of teacher adherence to the intervention.

The primary outcome, the d2-R concentration scores, will be analyzed in a three-level hierarchical linear model (West et al., 2022), with Age, Sex, and Performance at baseline included as covariates. The secondary outcome, well-being, will be analyzed in a similar fashion. Research question RQ1a will be tested with a comparison of the primary outcome variable between intervention group and control group measured at post-intervention. Research question RQ1b will be addressed with the same group comparison but based on the measurement of the primary outcome at follow-up. Research questions RQ2a and RQ2b involve the same group comparisons at post-intervention and follow-up, tested on the secondary outcome variable (child-reported well-being). We plan to test for the effect of the second level (classes within schools) and remove it from the model, if nested model comparisons do not significantly improve the model fit of the three-level model.

Exploratory analyses connected to RQ3 and RQ4 will include well-being questionnaires completed by parents and teachers, subdomains of d2-R and stop signal task performance, the intervention dosage if possible (e.g., number of lessons completed), and additional covariates.

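### The trial runs in a spring and an autumn wave, but the stated primary and secondary models have no wave term; adding one is a cheap gain in precision, mainly at follow-up

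*Protocol article*

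**What the plan says.** The Introduction (Phase III) of the protocol article splits delivery by season: "we plan to run the intervention in two waves (Wave 1 in the spring, and Wave 2 in the autumn". The same sentence ends with "testing intervention and control groups in parallel", and section 2.5 repeats that the arms are assessed side by side.

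Section 2.10 describes allocation of schools "using a computer-generated random sequence unavailable to those enrolling and assigning schools". It names no block or stratum. It also does not say whether all schools are drawn at once or wave by wave.

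Section 2.13 specifies a three-level hierarchical model for the d2-R score "with Age, Sex, and Performance at baseline included as covariates". Well-being is to be handled in a similar way, and the group comparison is made at post-intervention (t1) and at follow-up (t2). The further covariates mentioned in that section belong to the exploratory questions RQ3 and RQ4. Section 2.9 adds school size, grade average and absence as school-level covariates for the power calculation. Wave appears in neither list.

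The timing of t2 is given twice: "t_2_: 4 months after the intervention period (follow-up assessment" in section 2.5, and "take place 3-4 months after intervention completion" in section 2.8.

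**The concern.** Wave is a school-level factor that the investigators set themselves, and the model as stated ignores it. Schools in different waves are tested at different times of year. Counting forward 10 weeks plus three to four months, a spring start plausibly puts t2 after the summer break, and an autumn start puts it in the following spring. That is inferred from the calendar; the article does not say it. If pupils' change from baseline differs between waves, the difference goes to one of two places:

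- **Allocation not blocked by wave:** the arms can differ in wave mix by chance, and the estimate moves with them.
- **Allocation blocked by wave, wave left out of the model:** the estimate is protected, but wave variance inflates the standard error and the test is conservative.

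With 12 to 16 clusters, one school-level factor can matter. Table 4 sets the between-school variance share to 0.00, so it leaves no room for such a factor. That zero came from three schools (section 2.9) in a pilot run in a single autumn (Introduction), which could not have shown a difference between waves.

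**Working it through.** **Inputs from section 2.9 and Table 4.** Target effect 0.40; two-sided alpha 0.05; power 0.80; rho3 = 0.00; rho2 = 0.09; P = 0.50; R1² = 0.60; R2² = 0.20; R3² = 0.10; g3 = 1; n = 14 pupils per class; J = 2 classes per school; K = 12 schools needed, 16 to be recruited.

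**Assumptions, not in the article.** Equal waves (eight schools each when K = 16), and a wave shift w in SD units that remains after baseline adjustment, taken as 0.1 to 0.3.

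**1. Reproduce the plan's figure.** With rho3 = 0, the variance per school is

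V = rho2(1 − R2²)/J + (1 − rho2)(1 − R1²)/(J·n) = 0.09 × 0.80/2 + 0.91 × 0.40/28 = 0.036 + 0.013 = 0.049.

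SE = √[V/(P(1 − P)K)] = √(4 × 0.049/K), with df = K − g3 − 2.

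- K = 12: SE = 0.1278, df = 9, multiplier 3.146 (Table 4: 3.15), detectable effect 0.402, power 79.5%.
- K = 16: SE = 0.1107, df = 13, power 91.6%.

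The exact solution is K = 12.10, so the stated 12 stands, with rounding.

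**2. Leave wave out.** Two equal waves that differ by w add w²/4 to the between-school variance, so SE = √[4(0.049 + w²/4)/K] on the same df.

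| w (assumed) | w²/4 | Power, 16 schools | Power, 12 schools |
|---|---|---|---|
| 0 | 0 | 91.6% | 79.5% |
| 0.1 | 0.0025 | 90.2% | 77.5% |
| 0.2 | 0.0100 | 86.0% | 71.9% |
| 0.3 | 0.0225 | 79.0% | 63.7% |

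The table takes the wave variance in full. If Table 4's R3² of 0.10 is also applied to it, the 0.3 SD row becomes about 80% and 65%.

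These rows describe unblocked allocation. If schools are in fact blocked by wave but the term is omitted, a simulation of 16 school means at w = 0.3 gives a type I error of about 1.8% in place of 5%, and power of about 82%.

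**3. Chance imbalance if unblocked.** With 16 schools, eight per arm and eight per wave, the number of intervention schools in Wave 1 is hypergeometric with 12,870 possible allocations.

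- Exact 4:4 balance: 4,900/12,870 = 38.1%.
- 5:3 or worse: 100% − 38.1% = 61.9%.
- 6:2 or worse: 2 × (784 + 64 + 1)/12,870 = 13.2%.

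A 6:2 split makes the wave shares differ by 6/8 − 2/8 = 0.5, so the unadjusted estimate moves by 0.5w: 0.10 SD at w = 0.2 and 0.15 SD at w = 0.3, against a target of 0.40. Steps 2 and 3 are two views of one source of variance and should not be added together.

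**4. Put wave in the model.** This takes one further school-level df. With waves balanced between arms, power is 91.2% at 16 schools and 78.2% at 12, whatever w is. If a wave has already been allocated unevenly, the adjusted variance rises by 1/(1 − r²), where r is the difference in wave share. At 16 schools, r = 0.25 (5:3) gives 89.4% and r = 0.5 (6:2) gives 81.9%. This is why blocking is worth adding where it is still possible.

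**The case against.** The strongest reply is that this is a detail an article may leave to the full protocol or analysis plan, which may already block by wave and include the term. That stands for blocking: the silence in section 2.10 does not show unrestricted allocation, and a reader who infers one unblocked draw of all 16 schools goes beyond the text. It carries less weight for the model, because section 2.13 names its covariates outright and wave is not among them.

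A reader might also infer that season biases the arm comparison. The article does not support that. Both arms are tested in parallel, so imbalance could arise only by chance. Over repeated randomisation the estimate remains unbiased, and the model's school level carries wave variance into the standard error.

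The concern is weaker at t1. The interval from baseline to t1 is defined identically in both waves, and baseline and age are adjusted for, so a constant seasonal difference in level is largely absorbed. What remains is a difference in change, for which t2 is the more plausible place.

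The size of the wave effect is assumed throughout. At 0.1 SD or less the cost is negligible: about 90% power at 16 schools. A residual of 0.3 SD would be three quarters of the target effect.

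Finally, it is tempting to read the two t2 timings as a difference between waves. Nothing in the article ties them to wave; they are a separate inconsistency in wording.

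**Conclusion.** The point holds as a suggestion to improve precision. The stated models omit a known school-level design factor, and the article states no blocking on it. Given the assumed residual shift, the loss at 16 schools runs from about 1 power point (0.1 SD) to about 13 (0.3 SD); at 12 schools it runs from about 2 to about 16. These figures rest on equal waves, Table 4's variance inputs and a wave effect that the article does not supply, and they bear mainly on RQ1b and RQ2b. The point shows neither systematic confounding of arm with season nor an error in the sample size: on its own inputs, Table 4 reproduces.

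**What to change.** Add wave as a fixed effect to the t1 and t2 models for both the d2-R score and child-reported well-being, fixed before the data are analysed. For any wave not yet randomised, allocate schools 1:1 within wave and say so in section 2.10. If Wave 1 is already allocated, the model term can still be added.

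The cost is one school-level degree of freedom: power goes from 91.6% to 91.2% at 16 schools and from 79.5% to 78.2% at 12, with waves balanced. The solved number of schools moves from 12.10 to 12.36, which the planned 16 covers. If the full protocol or analysis plan already does this, a sentence confirming it is enough.

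Separately, reconcile the t2 timing in sections 2.5 and 2.8 so that one window applies to both waves.
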